### **9.22 End of Study/Early Termination Visit Follow Up Phase – Visit 7, Day 279 (+/- 30 days)**

- Physical and neurological examinations
- MDS-UPDRS (morning assessment)
- Vital signs (HR, BP, RR and T)
- Weight (morning assessment)
- ECG
- \*Optional lumbar puncture – if participant agrees to optional LP they will be followed up by a telephone call to assess any AEs and a concomitant medical review within 5 days of the visit.
- CSF collection enzyme activity & ELISA antibody panels if participant consents to the optional lumbar puncture procedure (if participant consents to LP)
- \*CSF ambroxol collection only if participant consents to optional lumbar puncture procedure (if participant consents to LP)

- \*\*Collecting IMP packaging, if early termination visit
- For female participants urine pregnancy test unless menopausal status is confirmed (if applicable)
- Blood collection enzyme activity, ELISA antibody panels
- Routine blood collection
- Urine collection (morning assessment)
- Collecting IMP packaging
- Adverse events review
- Concomitant medication review

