### 10.9 Overdose of Trial Medication

Should a participant take an overdose that exceeds the recommended dose described in the protocol and experiences any adverse event(s) that may relate to an overdose the participant must inform the PI or PI-delegated member of the research team immediately who will then follow up on their medical care as needed. It will be the opinion of the PI to decide whether the participant should be withdrawn from the study or whether the IMP should be reintroduced.

Each overdose will be recorded and the Sponsor will be notified of the overdose on the deviation log. Overdoses will be observed by the research team being instructed by the participant and pill counts on specific study visits, Visit 5 (day 93), Visit 6 (day 186) and the early termination visit, if applicable.

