### **10.12 Participant Stopping Criteria**

The stopping criteria refer to a participant stopping administration of the IMP. The withdrawal of a participant from the study may include the following reasons:

- Participants withdrawal of consent
- Non-compliance with the protocol
- Occurrence of an AE or change in medical status or an incidental finding that leads the Investigator concerned about the participant's welfare
- Pregnancy during the study
- Inability to continue, loss to follow-up
- The termination of the study by the Sponsor

If a participant is withdrawn from the study, they will be asked to undergo the early termination visit (visit 7, day 279) study procedures if applicable.

If enrolled participants prematurely discontinue the study or do not comply with the protocol, additional participants may be enrolled as replacement participants and assigned to the same treatment sequence at the discretion of the Principal Investigator. A maximum of two GBA positive and two GBA negative participants may be enrolled as replacement participants.

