### 10.16 Assessment of Compliance and Adherence

The participants will be instructed to return all (used and un-used) IMP packages at each clinic visit for compliance check. The returned IMP will be collected from the CI/PI or the PI-delegated member of the research team from the participant at Visit 5 (day 93) and Visit 6 (day 186). The returned IMP will be counted to assess compliance in addition to telephone visits 2-10 where IMP compliance will be assessed.

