iIf day 279 is early termination visit participants are expected to undergo all assessments for this visit and may consent to the optional lumbar puncture.

kIMP administered in clinic; see also f and i.

lPill count only, no packing collected.

mOnly conducted if participant agrees to optional lumbar puncture at visit 7.

nCollect packaging (no pill count) if this is early termination visit.

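### The protocol both requires and rules out a pill count at the early termination visit, so tablets taken since the last count may go uncounted in participants who stop early

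*Protocol*

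**What the plan says.** Four places in the protocol deal with counting or collecting returned study drug.

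- **Section 10.9 (overdose).** Overdoses are to be picked up from what participants report and from "pill counts on specific study visits, Visit 5 (day 93), Visit 6 (day 186) and the early termination visit, if applicable".
- **Appendix 1, footnote n.** This is attached to the Visit 7 cell of the row for packaging collection and pill count. It reads "Collect packaging (no pill count) if this is early termination visit".
- **Section 9.22 (Visit 7 / early termination).** The list includes "Collecting IMP packaging, if early termination visit". It has no pill count, no compliance item and no blood ambroxol sample.
- **Section 10.16 (compliance).** It opens with "The participants will be instructed to return all (used and un-used) IMP packages at each clinic visit for compliance check". It then names Visits 5 and 6 as the visits where returned drug is collected, and goes on: "The returned IMP will be counted to assess compliance in addition to telephone visits 2-10 where IMP compliance will be assessed".

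Sections 9.24 and 10.12 direct participants who leave early to Visit 7. For Visit 4, footnote l provides for a count ("Pill count only, no packing collected"), and Section 9.8 agrees.

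**The concern.** Section 10.9 and footnote n give opposite instructions for one procedure at one visit, so both cannot be followed. Section 8.6 tells staff to carry out the assessments shown in Appendix 1, and Section 9 refers to it for the detailed schedule. A site is therefore likely to work from the footnote and omit the check that Section 10.9 relies on.

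The gap is selective. Participants who complete treatment are counted at Visit 6, so only those who stop earlier are affected. Section 10.12 gives adverse events and non-compliance among the reasons for stopping, and Section 10.9 leaves withdrawal after an overdose to the investigator's judgement. These are the participants in whom departures from the prescribed intake are of most interest. Safety and tolerability is a secondary objective (Section 4.2), and how much drug an early leaver took is part of reading that participant's safety data.

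**Working it through.** The protocol states no figure for this point, so there is none to reproduce. The check sets the passages side by side and then sizes the consequence.

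**Inputs**

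- Tablets of 60 mg per day (table in Section 10.7): 3 on days 1-7, 6 on days 8-14, 9 on days 15-21, 15 on days 22-28, 21 on days 29-186.
- Counts before early termination: Visit 4 on day 9-11 (Section 9.8; Appendix 1, footnote l) and Visit 5 on day 93 (Sections 10.9 and 10.16).
- Compliance calls: telephone visits 2-10 (Section 10.16). In Appendix 1, call 9 falls on day 30-32 and call 10 on day 94-98.
- Assumptions: full adherence, nominal visit days, footnote n followed.

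**Scheduled tablets through day d, C(d)**

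- C(9) = 7×3 + 2×6 = 33 and C(11) = 7×3 + 4×6 = 45.
- C(28) = 7×(3 + 6 + 9 + 15) = 231.
- From day 29, C(d) = 231 + 21×(d − 28). So C(60) = 231 + 21×32 = 903, C(93) = 231 + 21×65 = 1596 and C(140) = 231 + 21×112 = 2583.

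**Tablets not covered by a count = C(stop day) − C(day of last count)**

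| Stop day | Last count | Scheduled tablets | Uncounted | Share |
|---|---|---|---|---|
| 28 | Visit 4 | 231 | 186-198 | 81-86% |
| 60 | Visit 4 | 903 | 858-870 | 95-96% |
| 92 | Visit 4 | 1575 | 1530-1542 | 97-98% |
| 107 | Visit 5 | 1890 | 294 | 16% |
| 140 | Visit 5 | 2583 | 987 | 38% |
| 185 | Visit 5 | 3528 | 1932 | 55% |

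For example, day 60 gives 903 − 45 = 858 to 903 − 33 = 870, and day 140 gives 2583 − 1596 = 987. The ranges reflect Visit 4 falling on day 9 or day 11.

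**Telephone cover.** Call 9 ends on day 32 and call 10 follows Visit 5. Days 33 to 92, that is 92 − 33 + 1 = 60 days, have no scheduled compliance call. After call 10 none is scheduled up to Visit 6.

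**If the count is done.** The uncounted share falls to zero for participants who attend the early termination visit and bring back their supply.

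**The case against.** The best case against the point is that it is a mismatch between the text and one footnote, with several safeguards around it. Much of this stands.

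- Section 10.16 can support 10.9. It asks for packages at every clinic visit, and its counting sentence is not limited to particular visits; only the collection sentence names Visits 5 and 6. Visit 7 is a clinic visit. This makes 10.16 ambiguous, but it does not cancel an explicit instruction not to count.
- A reader might infer that exposure is altogether unverified in those who stop early. The protocol does not support that. Visit 4 has a count, Visit 5 has one if it is reached, and blood ambroxol is drawn at both. Participants must also report an overdose with possibly related symptoms at once. Only intake since the last count is affected.
- Packaging is still collected, so tablets could be counted later. Section 10.6 leaves accountability to a separate drug arrangements document that is not available here and may cover this.
- A reader might take the cap of four replacements, out of 24 participants, as the share affected. The cap neither predicts nor limits departures, and no dropout rate is stated.
- A reader might also suppose that the uncounted time rests on telephone report alone. For about 60 days before Visit 5 no compliance call is scheduled.
- A count gives a net total for a supply period. It cannot date intake or tell an overdose from mislaid tablets, so it would not by itself link an adverse event to a dose taken.

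None of this reconciles Section 10.9 with footnote n, and no other section does so.

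**Conclusion.** The contradiction is real and is confined to one procedure. If footnote n is followed, intake since the last count is not verified by count in participants who stop early. For those who stop between Visit 4 and Visit 5 this can be nearly all of their tablets. For those who stop after Visit 5 it covers only the period from day 93.

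The tablet figures are scheduled amounts. Missed doses, or the dose reductions that Section 10.7 permits, would change actual intake, and the figures move with the visit windows. The number of participants affected cannot be estimated from the protocol.

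The consequence is for exposure and overdose data in early leavers. The primary outcome and the choice of sample size are untouched. It is an internal inconsistency worth correcting because it removes a check that the protocol's own safety text depends on.

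**What to change.** Reconcile the four places so that study drug returned at the early termination visit is counted, as Section 10.9 already assumes:

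- reword footnote n so that packaging is collected and a pill count is done;
- add the count to the list in Section 9.22;
- name the early termination visit in Section 10.16 beside Visits 5 and 6;
- leave the reference to that visit in Section 10.9 as it is, and check that the drug arrangements document agrees.

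The cost is counting tablets that are already being handed in, plus a wording amendment. No dose, stopping rule, visit or analysis changes.

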## Appendix 2 – UK Parkinson disease society brain bank clinical diagnostic criteria

### **UK PARKINSON'S DISEASE SOCIETY BRAIN BANK CLINICAL DIAGNOSTIC CRITERIA\***

#### **Step 1. Diagnosis of Parkinsonian Syndrome**

- Bradykinesia
- At least one of the following
  - Muscular rigidity
  - 4-6 Hz rest tremor
  - postural instability not caused by primary visual, vestibular, cerebellar, or proprioceptive dysfunction

#### **Step 2 Exclusion criteria for Parkinson's disease**

- history of repeated strokes with stepwise progression of parkinsonian features
- history of repeated head injury
- history of definite encephalitis
- oculogyric crises
- neuroleptic treatment at onset of symptoms
- more than one affected relative
- sustained remission
- strictly unilateral features after 3 years
- supranuclear gaze palsy
- cerebellar signs
- early severe autonomic involvement
- early severe dementia with disturbances of memory, language, and praxis
- Babinski sign
- presence of cerebral tumor or communication hydrocephalus on imaging study
- negative response to large doses of levodopa in absence of malabsorption
- MPTP exposure

#### **Step 3 supportive prospective positive criteria for Parkinson's disease**

Three or more required for diagnosis of definite Parkinson's disease in combination with step one

- Unilateral onset
- Rest tremor present
- Progressive disorder
- Persistent asymmetry affecting side of onset most
- Excellent response (70-100%) to levodopa
- Severe levodopa-induced chorea
- Levodopa response for 5 years or more
- Clinical course of ten years or more

*\*From: Hughes AJ, Daniel SE, Kilford L, Lees AJ. Accuracy of clinical diagnosis of idiopathic Parkinson's disease. A clinico-pathological study of 100 cases. JNNP 1992;55:181-184.*
